# General Practitioner Antimicrobial Stewardship Programme Study (GAPS): protocol for a cluster randomised controlled trial

**DOI:** 10.1186/s12875-016-0446-7

**Published:** 2016-04-21

**Keywords:** General practice, Primary care, Antimicrobial stewardship, Antibiotics, Antimicrobial resistance, Protocol

## Abstract

**Background:**

There is a strong link between antibiotic consumption and the rate of antibiotic resistance. In Australia, the vast majority of antibiotics are prescribed by general practitioners, and the most common indication is for acute respiratory infections. The aim of this study is to assess if implementing a package of integrated, multifaceted interventions reduces antibiotic prescribing for acute respiratory infections in general practice.

**Methods/design:**

This is a cluster randomised trial comparing two parallel groups of general practitioners in 28 urban general practices in Queensland, Australia: 14 intervention and 14 control practices. The protocol was peer-reviewed by content experts who were nominated by the funding organization.

This study evaluates an integrated, multifaceted evidence-based package of interventions implemented over a six month period. The included interventions, which have previously been demonstrated to be effective at reducing antibiotic prescribing for acute respiratory infections, are: delayed prescribing; patient decision aids; communication training; commitment to a practice prescribing policy for antibiotics; patient information leaflet; and near patient testing with C-reactive protein.

In addition, two sub-studies are nested in the main study: (1) point prevalence estimation carriage of bacterial upper respiratory pathogens in practice staff and asymptomatic patients; (2) feasibility of direct measures of antibiotic resistance by nose/throat swabbing.

The main outcome data are from Australia’s national health insurance scheme, Medicare, which will be accessed after the completion of the intervention phase. They include the number of antibiotic prescriptions and the number of patient visits per general practitioner for periods before and during the intervention. The incidence of antibiotic prescriptions will be modelled using the numbers of patients as the denominator and seasonal and other factors as explanatory variables. Results will compare the change in prescription rates before and during the intervention in the two groups of practices.

Semi-structured interviews will be conducted with the general practitioners and practice staff (practice nurse and/or practice manager) from the intervention practices on conclusion of the intervention phase to assess the feasibility and uptake of the interventions.

An economic evaluation will be conducted to estimate the costs of implementing the package, and its cost-effectiveness in terms of cost per unit reduction in prescribing.

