
### Sample size

The sample size calculation for this study was based on the average change in antibiotic prescription rates in practices in the intervention group (before – after the intervention) compared to the average change in practices in the control group over the same period. For example, an average change in antibiotic prescription rate from 40 to 20 % in the intervention practices and no change in the control practices would result in a difference of 0.2 between the two groups. A difference in average change in rates in the range 0.20–0.25, if the standard deviation in rates was about 0.2, was considered clinically significant and plausible. With equal numbers of practices in the two groups, power of 80 %, significance level of 5 % for a two tailed test, for a difference of 0.24, 12 practices per group would be needed. In fact 14 practices per group were recruited so that a difference of 0.22 would be detectable.

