### Randomisation

Practices were randomly assigned to either the intervention or control arm in a 1:1 ratio. A blocked randomisation list with 8 practices per block was generated using the online software package Sealed Envelope Ltd. 2015 available from: https://www.sealedenvelope.com/simple-randomiser/v1.

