### Data analysis

Prescription rates will be estimated using generalised linear models (e.g., Poisson regression) for the number of antibiotic prescriptions per GP in a specific period (e.g., day or week) with the number of patient encounters for that period and GP as the off-set (i.e., a measure of activity or ‘exposure’). The explanatory variables will be included in the model to account for: intervention vs control practices; periods before and during the intervention; and temporal variables to account for secular trends and seasonal effects. The models will be multi-level to account for nesting of patients within GPs and GPs within practices.

Cost-effectiveness of the package will be estimated from the perspective of the public healthcare system. Results will be presented as the net cost of implementation and as the cost per unit reduction in prescription rates. It is unclear what Australian decision makers are prepared to pay for a unit reduction in prescribing so results will be compared to cost-effectiveness estimates published in the international literature to gauge the efficiency of this package relative to other approaches used to reduce GP prescribing. Standard sensitivity analyses (one-way and probabilistic) will be used to explore the robustness of conclusions to uncertainty in the underlying data.

Semi-structured telephone interviews will be conducted with the GPs and practice staff, including practice nurses and/or practice manager, from the intervention practices, after the intervention phase of the study Questions will focus on the acceptability and feasibility of the interventions, including the near patient testing (CRP study) in the practice and perceived impact on the management of ARIs. Interviews will be conducted after the full package has been implemented. All interviews will be recorded digitally and transcribed verbatim by the interviewer. Interview data will be analysed using inductive thematic analysis. Two researchers will independently code the interviews, compare their coding and discuss discrepancies. The final thematic framework will be constructed through an iterative process and tested by researchers with clinical expertise.

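### The arms are compared on before-to-during change with no baseline adjustment named, which gives up some precision; how much depends on a correlation the protocol does not give

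*Protocol article*

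**What the plan says.** Three places in the protocol article bear on the contrast.

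- **Abstract, Methods/design:** "Results will compare the change in prescription rates before and during the intervention in the two groups of practices".
- **Sample size:** "The sample size calculation for this study was based on the average change in antibiotic prescription rates in practices in the intervention group", set against the same quantity in the control group. The effect regarded as worthwhile and realistic is given as "A difference in average change in rates in the range 0.20–0.25", on an assumed SD of about 0.2. The resulting figures are that "for a difference of 0.24, 12 practices per group would be needed", and that the 14 per group actually recruited make 0.22 detectable.
- **Data analysis:** a multilevel generalised linear model for prescription counts, with patient encounters as the offset. Its explanatory variables cover "intervention vs control practices; periods before and during the intervention", plus secular trend and season. No baseline-rate covariate is named, and no constraint that the arms share a baseline.

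Two further facts matter. Under Randomisation, "Practices were randomly assigned to either the intervention or control arm in a 1:1 ratio", in blocks of eight with no stratification described. Under Data collection, records are requested from July 2012 to the end of the intervention period.

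**The concern.** Comparing changes is the same as adjusting for baseline with the slope fixed at 1. Randomisation gives the arms the same expected pre-period rate, so there is no need to spend information on estimating a baseline difference between them. If the true slope of the during rate on the before rate is below 1, subtracting the whole baseline over-corrects. That adds noise to the estimate and leaves it exposed to whatever imbalance the draw produced.

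With 14 practices per arm, precision is scarce and a chance gap in baseline prescribing is likely to be noticeable. The data needed to deal with both are already part of the request. What is at stake is the width of the confidence interval and robustness to imbalance; the validity of the comparison is not in question.

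**Working it through.** **Inputs.** From Sample size: SD about 0.2; 80% power; two-sided 5%; 12 per group for 0.24; 14 per group for 0.22; target range 0.20 to 0.25. The before-during correlation r of practice rates is not in the document, so it is varied as an assumption.

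**1. Reproduce the plan's figures.** Two-sample t-test, noncentral t with 2n−2 df, noncentrality = d / (SD·√(2/n)), with 0.2 used as the SD of the practice-level change.
- n=12, d=0.24: noncentrality 0.24/(0.2·√(2/12)) = 2.94, power 80.2%. With n=11 it is 76.3%.
- n=14, d=0.22: noncentrality 0.22/(0.2·√(2/14)) = 2.91, power 80.0%.

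Both stated figures reproduce. On the same inputs, d=0.20 with n=14 has power 72.1%.

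**2. Variance of the two contrasts.** Let s be the common SD of practice rates before and during.
- Change: 2s²(1−r).
- Baseline-adjusted: s²(1−r²).
- Ratio, adjusted to change: (1+r)/2, which is below 1 for every r below 1.

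**3. Size of the gain, taking 0.2 as the SD of change.** Adjusted SD = 0.2·√((1+r)/2); n=14 per arm; 25 df.

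| r | Variance factor | Adjusted SD | Difference detectable at 80% | Power at 0.20 | Equivalent practices per arm, 14/factor |
|---|---|---|---|---|---|
| Change analysis | 1 | 0.200 | 0.220 | 72.1% | 14 |
| 0.5 | 0.75 | 0.173 | 0.191 | 83.5% | 18.7 |
| 0.7 | 0.85 | 0.184 | 0.203 | 78.8% | 16.5 |
| 0.8 | 0.90 | 0.190 | 0.209 | 76.4% | 15.6 |
| 0.9 | 0.95 | 0.195 | 0.215 | 74.2% | 14.7 |

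Under this reading, adjustment brings 0.20 to 80% power only if r is below about 0.65.

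**4. The other reading of the SD.** The text speaks of the SD in rates. If 0.2 is the SD of rates, the SD of change is 0.2·√(2(1−r)), which equals 0.2 only at r=0.5. Power at 0.20 from the change analysis alone is then about 81% at r=0.6, 91% at 0.7 and 98% at 0.8. With adjustment it is about 89%, 95% and 99%. The change analysis passes 80% once r exceeds about 0.59.

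**5. Unequal variances.** With SDs s₀ before and s₁ during, the change variance minus the adjusted variance is s₀²+s₁²−2r·s₀s₁−s₁²(1−r²) = (s₀−r·s₁)². This is never negative. It is zero when the regression slope r·s₁/s₀ equals 1.

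**6. Chance imbalance.** If rates have SD 0.2, the standard error of the baseline difference between arms is 0.2·√(2/14) = 0.076. Given a gap of one standard error, the change estimate is shifted by (1−r)·0.076: 0.038 at r=0.5 and 0.015 at r=0.8. Adjustment removes this shift.

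**The case against.** The strongest reply is that nothing here is wrong. Under randomisation a change contrast is valid and unbiased, and the choice is between two legitimate estimators. The model description offers its distribution and time unit only as examples, names no interaction and does not exclude a baseline covariate. In a condensed article, such detail is often left to the analysis plan. That stands in part. The Data analysis section alone would not settle the matter, but the abstract and Sample size both state the contrast as change, and nothing in the article points to adjustment.

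The second reply concerns size, and it stands in full. The gain depends on r, which is not given. A baseline of more than three years on the same GPs may measure each practice's usual rate so well that the slope is near 1, and step 5 shows the gain then disappears. The arithmetic also uses practice-level normal summaries, whereas the plan is a multilevel count model on the log scale.

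A reader might go further and infer that the change analysis leaves the low end of the target range under-powered and that adjustment repairs it. The document does not support this. It calls differences of 0.20 to 0.25 clinically significant and plausible but claims only 0.22 as detectable. Above r of about 0.65 the inference fails on either reading of the SD: either adjustment still leaves 0.20 short of 80%, so that the number of practices is the main limit, or the change analysis already exceeds 80%. Nor can r=0.5 be taken as the plan's own value. It follows only if 0.2 was meant as the SD of rates and then also used for the change, and the article shows no such step.

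**Conclusion.** The point holds as one of efficiency and robustness. The plan states the contrast that makes less use of data it will already hold. Baseline adjustment is at least as precise, apart from about one degree of freedom, and it removes the effect of chance imbalance among 28 practices.

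The variance saving is 25% at r=0.5, 15% at 0.7, 10% at 0.8 and 5% at 0.9. This assumes equal variances before and during and a practice-level normal summary; the planned count model would follow it only approximately. With r unknown, no single figure should be quoted, and the gain may be small. The stated sample size is arithmetically sound, and adjustment may or may not bring a difference of 0.20 to 80% power.

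**What to change.** Prespecify as the primary effect the during-period rate ratio between arms, adjusted for each practice's (or GP's) pre-intervention log rate. Taking that rate from the same calendar months of earlier years would keep season aligned. Alternatively, fit the multilevel model with the pre-period arm difference constrained to zero and random practice-by-period effects. In a count model the two are close but not identical, so one should be named. State the value or range of r assumed, and whether the SD of 0.2 refers to rates or to change. Keep the unadjusted change comparison as a sensitivity analysis.

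The cost is about one degree of freedom and slightly more modelling, with no new data. The article says the Medicare data are accessed only after the intervention phase, and that the six-month period was under way at publication, so the change could be made before outcomes were seen.

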**Discussion:**

The results on the effectiveness, cost-effectiveness, acceptability and feasibility of this package of interventions will inform the policy for any national implementation.

**Trial registration:**

The GAPS trial is registered under the Australian New Zealand Clinical Trials Register, reference number: ACTRN12615001128583 (registered 26/10/2015).

## Background

Australia is one of the highest consumers of antibiotics in the developed world with 45 % of the Australian population being supplied at least one antibiotic per year [1]. The defined daily dose (DDD) in Australia is nearly 23/1000 population/day [1] compared with about 18 DDD/1000 population /day in Denmark and less than 11 DDD/1000 population /day in general practice in the Netherlands [2–4].

There is a strong link between antibiotic consumption and the rate of antibiotic resistance [5]. Acute respiratory tract infection (ARIs) are the most common reason for prescribing an antibiotic in primary care [6]. In Australia antibiotic resistance in common pathogens causing ARIs has increased over the past 20 years [7]. For example, resistance of *Streptococcus pneumoniae* to macrolide antibiotics has increased from 8.7 % in 1994 to 20.4 % in 2007, and this trend is continuing [8]. Patients with infections caused by antibiotic-resistant organisms have an increased mortality compared with those infected with antibiotic-susceptible organisms [9, 10].

General Practitioners (GPs) have the potential to be the most influential health care professionals to address the problem of antibiotic resistance as the majority of antibiotics are prescribed in the general practice setting and antibiotics remain the most common class of medicine prescribed [11]. Continued improvements in prescribing practice and a positive influence on individual and community beliefs about antibiotic consumption are essential to limit the spread of antibiotic resistance [12]. Antibiotics are often inappropriately prescribed for patients with ARIs [6]. Research shows that up to half of antimicrobials prescribed in Australian hospitals are discordant with guidelines or microbiological results and hence are considered inappropriate,[13] however, little is known about what happens in the primary care setting [14].

Unfortunately, new antimicrobials are not being developed at a pace that comes anywhere close to meeting the urgent need; therefore, the healthcare system needs to undertake efforts that save one of medicine’s most precious and long-standing resources [15]. This was summarised by the World Health Day 2011 slogan ‘Combat antibiotic resistance: no action today, no cure tomorrow’. Reducing the inappropriate use of antimicrobials has been shown to improve patient outcomes and reduce adverse consequences of antibiotic use (including antibiotic resistance, toxicity and unnecessary costs) [16].

Antimicrobial stewardship (AMS) is the coordinated actions designed to promote and increase the appropriate use of antimicrobials and is a key strategy to conserve the effectiveness of antibiotics. Australia’s first National Antimicrobial Resistance strategy for 2015–2019 states that there is a need for resources to support the implementation of AMS for all settings including primary health care [17].

There are a number of interventions that have shown promise at decreasing antibiotic prescribing for ARIs in primary care: delayed prescribing; patient decision aids; communication training; near patient testing with C-reactive protein and commitment to a practice prescribing policy for antibiotics [18–20]. Prescribers are well placed to convey the importance of informing patients that they are twice as likely to carry resistant bacteria after a course of antibiotics as someone who has not taken them [21–23]. Evidence from general practice demonstrates that patient satisfaction is linked more with good communication than a prescription for an antibiotic [24, 25]. Several studies have demonstrated that GPs trained in communication skills, [26, 27] and specifically in Shared Decision Making [28–30], prescribed antibiotics significantly less than GPs without training. The benefits of patients managed by a GP trained in enhanced communication skills can persist for at least 3 years, and do not appear to compromise repeat consultation rate, patient recovery or patient satisfaction [26, 27, 31, 32].

Many of these strategies have not been adopted in Australia so there is no evidence about their efficacy in this context, and all have been evaluated in isolation. Evidence from other areas of healthcare suggests that using multiple strategies or interventions in concert could have an even greater impact on prescribing behaviour and induce longer term behaviour change. This could enable clinicians and health care systems to reduce antimicrobial resistance in the future [33].

### Aim

The aim of our study is to assess if implementing an integrated, multifaceted package of interventions reduces antibiotic prescribing for ARIs in general practice.

### Sub-studies nested within the main study

Two specific studies are nested in the main study:point prevalence estimation carriage of bacterial upper respiratory pathogens in practice staff and asymptomatic patientsfeasibility of direct measures of antibiotic resistance by nose/throat swabbing.

### Primary objective

Our primary objective is to assess the effectiveness, of an integrated, multifaceted package of interventions for ARIs in general practice.

### Secondary objectives are

to assess the feasibility and uptake of the integrated package of interventions for ARIs.to assess the likely costs and cost-effectiveness of implementing the integrated package of interventions for ARIs.to estimate the prevalence of bacterial upper respiratory pathogens in asymptomatic general practice staff and patientsto assess the feasibility of direct measures of antibiotic resistance by nose/throat swabbing.

## Methods

The trial protocol was developed by researchers at the University of Queensland, Bond University and Queensland University of Technology in Australia in accordance with the CONSORT statement extension to cluster randomised trials [34].

### Study design

This is a clustered randomised parallel group controlled trial.

### Study setting

This study is being conducted in South East Queensland, Australia. Twenty-eight urban general practices have been purposely recruited and randomised to either the control or intervention group.

### Eligibility criteria

All GPs from the recruited general practices were eligible to participate in the study provided they gave consent for the research team to obtain their data on antibiotic prescribing and patient visits from Medicare. General practice staff and patients attending the GP practice for consultation with non-infectious complaints were eligible for the point prevalence nose and throat swab study: asymptomatic carriage of bacterial upper respiratory pathogens.

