### Sub-studies

Specific studies are nested in the main study: (1) 1 point prevalence nose and throat swab study: asymptomatic carriage of bacterial upper respiratory pathogens; (2) feasibility of direct measures of resistance by nose/throat swabbing.*Point prevalence nose and throat swab study: asymptomatic carriage of bacterial upper respiratory pathogens*This pilot study seeks to assess the prevalence of common bacterial upper respiratory tract commensals and pathogens in the nose and throat swabs of general practice staff and patients attending the GP practice for consultation with non-infectious conditions; and the rate of antimicrobial resistance in organisms isolated. It is not clear whether general practice settings are more like hospital settings, where staff can have a higher risk of carriage of resistant organisms; or more like the community, with staff having similar carriage and resistance patterns to asymptomatic adults. Properly addressing this question will have implications for the sort of infection control practices necessary in General Practice settings.Anterior nasal and throat swabs will be taken from selectively recruited general practice staff and patients who have consented to be part of the sub-study. A total of 125 general practice staff and 125 patients across the practice sites will be included.Various appropriate bacterial media will be used to capture both potential pathogens and normal flora. The swabs will be cultured on selective media, such as mannitol salt agar and MacConkey agar to screen for *Staphylococcus aureus* and Gram-negative bacteria of respiratory pathogens such as *Klebsiella pneumoniae* and *Pseudomonas aeruginosa* [40]. Organisms isolated will be further evaluated for resistance to commonly used antibiotics with standard susceptibility testing [41]. Antibiotic resistant organisms will also undergo molecular characterisation to look for potential clonality and spread in the community [42].*Rolling out community antibiotic resistance surveillance: ASPReN pilot*The study will assess the feasibility of surveillance of antibiotic resistance in primary care on a national basis utilising the Australian Sentinel Practice Network (ASPReN). ASPReN is a national network of GPs involved in surveillance activities including influenza. ASPReN will identify general practices in their network and provide simple instructions for taking and transporting throat and nasal swabs (Fig. 1). ASPReN will provide feedback about the feasibility of this surveillance activity.

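### The swab sub-study's printed entry rule does not secure the asymptomatic status its objective requires, and the article is inconsistent on whether staff must be asymptomatic

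*Protocol article*

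**What the plan says.** All references are to the protocol article.

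- **Objective.** The third item under Secondary objectives is the prevalence of upper respiratory pathogens in practice staff and patients. The word asymptomatic stands directly before staff.
- **Sub-study title.** The abstract (Methods/design) words it as "point prevalence estimation carriage of bacterial upper respiratory pathogens in practice staff and asymptomatic patients", and the section on nested sub-studies repeats this. Here asymptomatic qualifies patients only.
- **Entry rule.** Eligibility criteria: "General practice staff and patients attending the GP practice for consultation with non-infectious complaints were eligible for the point prevalence nose and throat swab study". The sentence ends by naming the target as "asymptomatic carriage of bacterial upper respiratory pathogens". Recruitment and Sub-studies repeat the rule in similar words.
- **Question behind it.** Sub-studies asks whether practice staff resemble hospital staff, who can be at higher risk of carrying resistant organisms, or the community, "with staff having similar carriage and resistance patterns to asymptomatic adults". It says the answer bears on infection control in general practice.
- **Scale and status.** "This pilot study seeks to assess the prevalence of common bacterial upper respiratory tract commensals and pathogens". Resistance in the organisms isolated is also a target. The size is 125 staff and 125 patients, with no derivation given.
- **Antibiotic exposure.** Background says of patients that "they are twice as likely to carry resistant bacteria after a course of antibiotics as someone who has not taken them", and reports "45 % of the Australian population being supplied at least one antibiotic per year".

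**The concern.** The condition that defines the target population is absence of symptoms. The condition applied at the site is the reason for today's visit, and it applies to patients only. These are different things. As printed, a staff member with a current cold qualifies. So does a patient attending for blood pressure who also has a sore throat, and so does a child attending for a non-infectious complaint.

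Two results are at stake. First, a group's prevalence can be reported as asymptomatic carriage only if somebody checked for symptoms. Second, the question posed under Sub-studies needs staff to be set against people who do not work in general practice, and the 125 patients are the only such group in this sub-study. If the groups differ in symptoms, age or recent antibiotic use, a difference between them need not come from the workplace.

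**Working it through.** **1. The passages side by side**

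| Place | Symptom condition on staff | Symptom condition on patients | Age limit |
|---|---|---|---|
| Secondary objectives | asymptomatic | asymptomatic (natural reading) | none |
| Abstract; nested sub-studies | none | asymptomatic | none |
| Eligibility criteria; Recruitment; Sub-studies (entry rule) | none | none; reason for consultation only | none |
| Sub-studies (rationale) | not stated | comparator is asymptomatic adults | adults |

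The entry rule matches neither statement of the target. The two statements also disagree about staff, who are 125 of the 125 + 125 = 250 people to be swabbed.

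**2. What can be said about size**

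*Symptoms and age.* The article gives no share of symptomatic participants, no carriage ratio for symptomatic against asymptomatic people, and nothing by age. No size can be calculated.

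*Recent antibiotics.* The article gives one ratio, about 2 (Background). It gives no recent exposure by group; the 45% is annual supply in the whole population and serves here only as an upper bound. Let r be the prevalence of resistant carriage in people not recently exposed and a the share recently exposed. Then

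group prevalence = r(1 − a) + 2ra = r(1 + a).

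With no true staff-patient difference, the spurious ratio is (1 + a_patients)/(1 + a_staff). The 95% half-width of the difference is 1.96 × √[p_s(1 − p_s)/125 + p_p(1 − p_p)/125], where p_s and p_p are the staff and patient prevalences. The values of r and both values of a are assumptions.

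| a staff | a patients | Ratio | r | Staff | Patients | Spurious difference (points) | 95% half-width (points) |
|---|---|---|---|---|---|---|---|
| 10% | 10% | 1.10/1.10 = 1.00 | 5% | 5.5% | 5.5% | 0 | 5.7 |
| 10% | 25% | 1.25/1.10 = 1.14 | 5% | 5.5% | 6.25% | 0.75 | 5.8 |
| 10% | 25% | 1.14 | 10% | 11.0% | 12.5% | 1.5 | 8.0 |
| 0% | 45% | 1.45/1.00 = 1.45 | 5% | 5.0% | 7.25% | 2.25 | 5.9 |
| 0% | 45% | 1.45 | 10% | 10.0% | 14.5% | 4.5 | 8.1 |

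The last two rows are a deliberate extreme. In every row the spurious difference is smaller than the half-width. That does not make it harmless, because an interval does not allow for bias. In the third row the standard error is 8.0/1.96 = 4.1 points, so the bias is 1.5/4.1 = 0.37 standard errors, and nominal 95% coverage falls to Φ(1.96 − 0.37) − Φ(−1.96 − 0.37) = about 93%.

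This models resistant carriage per person. The article's resistance measure is taken among isolates, so the table shows direction and order of magnitude only.

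**The case against.** The strongest reply is that the article tells its reader what is meant. The eligibility sentence ends by naming asymptomatic carriage, Recruitment repeats this, and a condensed article may leave the symptom screen, look-back window and age limit to the full protocol. The sub-study is a descriptive pilot with no formal staff-patient test, and the person with a cold, the one with a sore throat and the child are hypothetical.

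Part of this stands. Silence about antibiotic use in a condensed article is not a finding in itself, and no passage says that symptomatic people are to be swabbed. But the entry rule is not left out. It is printed under three headings in a form that does not deliver the stated target, and the printed targets differ on staff. Naming the target in the study title is not a criterion that a site can apply.

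Three stronger readings are tempting, and the document supports none of them:

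- A reader might infer that the objective specifies adults. It does not; the word occurs only in the rationale, as the community comparator.
- A reader might infer that the prevalence estimates are confounded by antibiotic use. A single group's prevalence is descriptive, and recent users belong to the attending population. Only an occupational reading of the staff-patient contrast could be confounded this way, and only if exposure differs between the groups, which nothing in the article shows.
- A reader might conclude that recent users should be excluded. That would change the population being described.

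**Conclusion.** The point holds as a mismatch between printed statements. The entry rule does not secure the asymptomatic status that the objective requires, and the article is inconsistent on whether staff must be asymptomatic. It follows that a staff-patient difference, if reported, could reflect symptoms, age or differing antibiotic use as well as the workplace.

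The size of any such bias cannot be determined from the document. The antibiotic illustration runs from a ratio of 1.00 with equal exposure to 1.45 at the extreme. It rests on assumed exposure shares, an assumed baseline prevalence, and the article's doubling read as a prevalence ratio. It does not show that bias is present.

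The consequence is confined to one secondary objective of pilot status. The randomised comparison and the primary outcome are not affected.

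**What to change.** 1. Reconcile the sub-study title in the abstract and in the nested sub-studies section with the secondary objective, so that all say the same about staff.
2. Apply one rule to both groups: no acute respiratory symptoms on the day of swabbing, checked at consent.
3. Record age and recent systemic antibiotic use, over a fixed look-back window, on the swab form.
4. Report each group's overall prevalence as planned. Base any staff-patient comparison on adults, with an estimate adjusted for, or stratified by, age and recent antibiotic use alongside.
5. Recruitment describes participants as already recruited, whereas Sub-studies describes swabbing as still to come, so some collection may still be correctable. For anyone already swabbed without a symptom record, the rule cannot be applied afterwards; the report should say that asymptomatic status was not verified.

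The cost is a few form items and one extra table. A few people will be excluded, and the intervals will be slightly wider.
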